#### 7.5 Replacement of individual subjects after withdrawal

Patients that meet inclusion criteria will be invited for participation in the study. When patient agrees to participate in the study, informed consent is signed and the patient will enrol in the wash-out period. The patient is included in the study when blood pressure values are within the predefined window (see paragraph 3). When patients decide to

withdraw after start of the treatment period, no new patients can be admitted to the study due to a limited availability of study medication. Although, in our sample size calculation we have taken into account a certain amount of withdrawal and according to our experience, we don't expect withdrawal to exceed this number.

#### **7.6 Follow-up of subjects withdrawn from treatment**

Subjects who withdraw from the study will be followed up according to the routine terms of patient care at the outpatient clinic or referred back to their general practitioner.

#### **7.7 Premature termination of the study**

There are no predefined criteria for premature termination of the study. If, however, during the conductance of the study information becomes available showing that continuation of the study would result in a significant safety risk for the patients, the principal investigator and project leader will decide to terminate the study.

## 8 SAFETY REPORTING

### 8.1 Section 10 WMO event

In accordance to section 10, subsection 1, of the WMO, the investigator will inform the subjects and the reviewing accredited METC if anything occurs, on the basis of which it appears that the disadvantages of participation may be significantly greater than was foreseen in the research proposal. The study will be suspended pending further review by the accredited METC, except insofar as suspension would jeopardise the subjects' health. The investigator will take care that all subjects are kept informed.

### 8.2 Adverse and serious adverse events

Adverse events are defined as any undesirable experience occurring to a subject during a clinical trial, whether or not considered related to the investigational drug. All adverse events reported spontaneously by the subject or observed by the investigator or his staff will be recorded.

A serious adverse event is any untoward medical occurrence or effect that at any dose results in death;

- is life threatening (at the time of the event);
- requires hospitalisation or prolongation of existing inpatients' hospitalisation;
- results in persistent or significant disability or incapacity;
- is a congenital anomaly or birth defect;
- is a new event of the trial likely to affect the safety of the subjects, such as an unexpected outcome of an adverse reaction, lack of efficacy of an IMP used for the treatment of a life threatening disease, major safety finding from a newly completed animal study, etc.

All SAEs will be reported to the accredited METC that approved the protocol, according to the requirements of that METC.

#### 8.2.1 Suspected unexpected serious adverse reactions (SUSAR)

Adverse reactions are all untoward and unintended responses to an investigational product related to any dose administered.

Unexpected adverse reactions are adverse reactions, of which the nature, or severity, is not consistent with the applicable product information (e.g. Investigator's

Brochure for an unapproved IMP or Summary of Product Characteristics (SPC) for an authorised medicinal product).

The sponsor will report expedited the following SUSARs to the METC:

- SUSARs that have arisen in the clinical trial that was assessed by the METC;
- SUSARs that have arisen in other clinical trial of the same sponsor and with the same medicinal product, and that could have consequences for the safety of the subjects involved in the clinical trial that was assessed by the METC.

The remaining SUSARs are recorded in an overview list (line-listing) that will be submitted once every half year to the METC. This line-listing provides an overview of all SUSARs from the study medicine, accompanied by a brief report highlighting the main points of concern.

The sponsor will report expedited all SUSARs to the competent authority, the Medicine Evaluation Board and the competent authorities in other Member States.

The expedited reporting will occur not later than 15 days after the sponsor has first knowledge of the adverse reactions. For fatal or life threatening cases the term will be maximal 7 days for a preliminary report with another 8 days for completion of the report.

There will be three sets of emergency code breaks, one set will be retained by the project leader, one set will be retained by the principal investigator and a set will be forwarded to the pharmacy. The blinded emergency code break contains the details of drug treatment. In an emergency, the code can be unblinded to identify the treatment given to that subject. Unblinding is not to be performed for any reason, other than an emergency where unblinding is required. When the Investigator removes the scratch-off covering he/she must note the date, time and reason for removing it and record this information in the Comments section of the CRF/ on the code-break card (source data). He/she must also immediately inform the project leader and the principal investigator that the code has been broken. Even though the code is broken, any blood samples for safety, pharmacokinetic and pharmacodynamic assessments will continue to be drawn, for at least 24hr following the last dose as long as doing so will not compromise subject welfare.

It is the responsibility of the Investigator to ensure that there is a procedure in place to allow access to the code break cards in case of emergency. Study drug must be discontinued after unblinding but the subject will be followed until resolution of the

adverse event. At the conclusion of the study, the occurrence of any emergency code breaks will be determined after return of all code break reports.

### **8.2.2 Annual safety report**

In addition to the expedited reporting of SUSARs, the sponsor will submit, once a year throughout the clinical trial, a safety report to the accredited METC, competent authority, Medicine Evaluation Board and competent authorities of the concerned Member States.

This safety report consists of:

- a list of all suspected (unexpected or expected) serious adverse reactions, along with an aggregated summary table of all reported serious adverse reactions, ordered by organ system, per study;
- a report concerning the safety of the subjects, consisting of a complete safety analysis and an evaluation of the balance between the efficacy and the harmfulness of the medicine under investigation.

### **8.3 Follow-up of adverse events**

All adverse events will be followed until they have abated, or until a stable situation has been reached. Depending on the event, follow up may require additional tests or medical procedures as indicated, and/or referral to the general physician or a medical specialist.

### **8.4 Data Safety Monitoring Board (DSMB)**

The institution of a DSMB is not suitable to improve the safety of the patients as this is a cross-over study with study duration of only 26 weeks. The absence of a DSMB has been approved in a comparable study of our department (ARIA-study: METc 2010.114). The safety profile of aliskiren has been well characterized and investigated in completed clinical trials that involved 15.000 hypertensive patients. Specific stopping rules for hyperkalemia and hypotension are defined in the protocol to safeguard patients.

## STATISTICAL ANALYSIS

### **8.5 Descriptive statistics**

Patients will be described with their demographical and medical data. Further, all outcome variables will be evaluated with descriptive statistical methods. Results will be expressed as median and 95% confidence interval for not-normally distributed parametric data. Normal parametric data will be expressed as mean and standard deviation. A two-sided *P*-value less than 0.05 will be considered statistical significant.

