## 1. INTRODUCTION AND RATIONALE

The combination of hypertension and obesity is a highly prevalent clustering of cardiovascular risk factors which considerably contributes to over-all morbidity and mortality in the general population. The kidneys play a central role in the interaction between these two risk factors.

Obese or overweight hypertensive patients have increased glomerular pressure (1), which is considered a driving force for progressive end-organ damage of the kidney (2), thus contributing to the vicious circle of hypertension and target organ damage. In line, weight excess is an independent risk factor for renal damage that adds to the effect of elevated blood pressure (3;4). Accordingly, specific correction of increased glomerular pressure, on top of reduction of systemic blood pressure, has been shown to be renoprotective in experimental animals and in renal patients (5;6). Glomerular pressure is determined by the net balance between the tone of the afferent and efferent glomerular vessels and is mainly regulated by the Renin Angiotensin Aldosterone System (RAAS) that modifies efferent vascular tone. This is particularly relevant given the availability of antihypertensive drugs that specifically interfere in the RAAS, i.e. the ACE-inhibitors (ACEi), the Angiotensin Receptor Blockers (ARB) and specific renin-inhibition. Based on these considerations it is likely that the renal hemodynamic actions of RAAS-blockade will be of specific benefit in overweight or obese hypertensive patients.

Aliskiren represents the new class of direct renin inhibitors, i.e. blockade of the RAAS at its point of activation. Importantly, the effects of aliskiren on glomerular pressure have not been tested so far. A beneficial short term (decrease of glomerular pressure) and long term (prevention of end stage renal disease) renal profile has been proven with the older RAAS blocking drug classes (ACEi, ARB) (7). It seems logical to assume that aliskiren will decrease glomerular pressure as well, in particular because renin-inhibition with older renin-inhibitors was shown to have more potent renal effects than ACEi and ARB. In our hands renin-inhibition with remikiren was shown to reduce glomerular pressure in hypertensive and normotensive volunteers (8).

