### **Research question:**

Does aliskiren ameliorate glomerular hypertension in overweight/obese hypertensive patients, in addition to its effect on blood pressure?

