#### 4.4 Sample size calculation

We hypothesized that patients will present a mean $\pm$ SD ERPF of 444 $\pm$ 35 ml/in at baseline (i.e. after discontinuation of antihypertensive medication). Assuming an increase of 13 $\pm$ 11 ml/min with ACEi (10) and an increase of 47 $\pm$ 17 ml/min with aliskiren (11), it was estimated that 14 patients had to complete the cross-over design sequence to give the study a 90% power to detect a statistically significant difference ( $\alpha=0.05$ ). On the basis of an expected dropout rate of 10% due to the possibility of side effects in patients on aliskiren or ramipril, 16 patients will be included in this study.

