## 7 METHODS

### 7.1 Study parameters/endpoints

#### 7.1.1 Primary study parameters

- Renal hemodynamics (GFR, ERPF, FF)
- Blood pressure

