#### Blood pressure measurements

At start and end of each treatment period, blood pressure is measured over a period of 24hr by an ambulant device (Spacelab). Furthermore, blood pressure is measured at 1-minute intervals for 15 minutes with a semi-automatic device (Dinamap; DE Medical systems, Milwaukee, WI) at study inclusion and during renal hemodynamic measurements. In addition, blood pressure is measured 2 weeks after start of each treatment period and 3 weeks after start of each wash-out period.

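### Two sections name different primary endpoints, all judged at 0.05 with no deciding variable or order, and only ERPF has a sample size

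*Protocol*

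**What the plan says.** The research question in section 2 is "Does aliskiren ameliorate glomerular hypertension in overweight/obese hypertensive patients, in addition to its effect on blood pressure". Section 7.1.1, like the Summary, answers with two primary items: "Renal hemodynamics (GFR, ERPF, FF", and blood pressure. Section 8.6 gives a different list. Set side by side:

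| Variable | Summary, 7.1.1, 7.1.2 | 8.6 | Effect and SD in 4.4 |
|---|---|---|---|
| GFR | primary | primary | none |
| ERPF | primary | primary | yes |
| FF | primary | primary | none |
| Blood pressure | primary | not named | none |
| ECV | secondary | primary | none |

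Section 8.5 sets one criterion for all outcomes: a two-sided P-value "less than 0.05 will be considered statistical significant". Section 4.4 derives 14 completers "to give the study a 90% power" from assumed ERPF changes on the two drugs, and includes 16 to allow for 10% dropout. The document gives no order of testing, no division of alpha, no single deciding variable and no rule that all primaries must be significant.

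**The concern.** A reader of the final report could not tell from this protocol which result decides the trial. Blood pressure is primary in two places and absent from the primary list in the statistics section; ECV is the reverse. Three renal variables stand on both lists with equal rank, although only one of them was used to size the trial.

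Two things are at stake. The first is the error rate. With four or five equally ranked variables at 0.05 each, a result on whichever variable happens to be significant could be presented as the primary finding. The second is power. The 90% holds for ERPF only, and nothing is known about the other variables that share its status.

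**Working it through.** **Step 1. The protocol's own figure.** Inputs from section 4.4: ERPF change +13 (SD 11) ml/min on ACE inhibitor, +47 (SD 17) on aliskiren, baseline SD 35, alpha 0.05, power 90%.

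- Difference between drugs: 47 - 13 = 34 ml/min.
- Paired t-test, noncentrality = (34/SD) × √n. The SD of the paired difference is not stated. Taking it as 35: at n = 14, (34/35) × √14 = 3.63, power 91.9%; at n = 13, power 89.5%. So n = 14, as stated.
- Dropout: 14/0.90 = 15.6, rounded up to 16, as stated.

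The figure reproduces, for ERPF, with 35 used as the SD of the paired difference. No such calculation can be made for GFR, FF, blood pressure or ECV.

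**Step 2. Error rate if any one significant primary counts, tests independent.** Formula: 1 - 0.95^k.

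- k = 4 (either list): 1 - 0.8145 = 18.5%.
- k = 5 (both lists combined): 1 - 0.7738 = 22.6%.

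**Step 3. Allowing for dependence.** Section 7.3 calculates FF as GFR/ERPF, so on the log scale FF = GFR - ERPF, and the three renal tests overlap. Simulation under no treatment difference: paired t-tests, n = 14, one test per variable, 100,000 trials per setting (Monte Carlo standard error about √(0.17 × 0.83/100,000) = 0.1 percentage point). The correlations are assumptions, because the protocol gives none: GFR with ERPF 0 to 0.9; ratio of GFR to ERPF SD 0.6 or 1; blood pressure and ECV correlated 0 or 0.3 with ERPF and with each other.

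| Variables tested | At least one P < 0.05 |
|---|---|
| GFR, ERPF, FF | 9.6-12.6% |
| Either list of four | 13.8-17.1% |
| All five | 17.7-21.3% |

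**Step 4. Error rate if all must be significant.** Under that rule the type I error does not exceed 5%. Joint power cannot exceed the lowest power among the four variables, and for three of them no effect or SD is given. The "90% power to detect a statistically significant difference" in section 4.4 would then describe ERPF alone and not the trial.

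**Step 5. What the remedies cost in ERPF power** (difference 34, SD 35).

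| Approach | Alpha for ERPF | Power, 14 completers | Completers for 90% | Included (÷ 0.90) |
|---|---|---|---|---|
| ERPF alone or first in sequence | 0.05 | 91.9% | 14 | 16 |
| Bonferroni over four | 0.0125 | 75.6% | 19 | 22 |
| Bonferroni over five | 0.01 | 72.2% | 20 | 23 |

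**The case against.** The strongest reply is that the statistical analysis plan is not at hand, and hierarchies and alpha splits are commonly left to it. A single 0.05 threshold is also conventional wording. That is fair as far as the mechanics go. It does not cover the choice of primary variable, which belongs to the protocol and on which the protocol contradicts itself. An analysis plan could only follow one list by overriding the other.

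Three stronger readings are tempting and are not supported.

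- A reader might infer that the trial succeeds if any one primary is significant, or that the variables are co-primary so that all must be. The protocol says neither. The error rates in steps 2 and 3 are therefore conditional on the first reading.
- A reader might infer that, by the protocol's own physiology, ERPF cannot show a fall in glomerular pressure and FF must. The Introduction says only that "Glomerular pressure is determined by the net balance between the tone of the afferent and efferent glomerular vessels", then stresses efferent tone as regulated by the RAAS. It does not rank FF above ERPF. That ranking would be an outside inference.
- A reader might add further blood pressure tests, because section 7.3 describes both the ambulatory recording and a semi-automatic device, and inclusion criteria speak of systolic and diastolic values. The protocol does not say that each is tested as a primary, so they are not counted here.

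It can also be argued that strict familywise control is demanding for a 16-patient mechanistic crossover, and that putting ERPF first blocks a confirmatory claim on FF when ERPF is null. The second consequence is real and is counted as a cost below. The first argument bears on how strict the control should be. It does not excuse two different primary lists.

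**Conclusion.** The concern holds. The protocol contains two conflicting lists of four primary endpoints, one threshold for all of them, no deciding variable or order, and a sample size for ERPF only. These facts need no assumption.

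The size of the problem does. If any one significant primary were read as a positive result, the chance of at least one false positive would be about 14-17% for either list and about 18-21% for the five variables that the two lists name together, instead of 5%. Full independence would give 18.5% and 22.6%. The five-variable figure applies only if both lists are honoured, since no single section names five. If all had to be significant, alpha would be protected but the 90% power would not apply. Under either rule, the trial's conclusion lacks the error rate or the power that the protocol appears to offer. This should be corrected; the correction is one of wording and needs no redesign.

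**What to change.** 1. Make the Summary, 7.1.1, 7.1.2 and 8.6 agree on one list.
2. Name the aliskiren-ramipril difference in ERPF as the single primary endpoint, because it is the only variable with a sample size.
3. Test FF and then GFR in fixed sequence at two-sided 0.05, each only if the preceding test is significant.
4. Report blood pressure (24-hour ambulatory, section 7.3: "blood pressure is measured over a period of 24hr by an ambulant device (Spacelab") and ECV as secondary, with confidence intervals and no confirmatory claim.
5. State that power for FF and GFR is not established.

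The 14 completers and 16 included remain as planned. That suits this trial, because section 7.5 already rules out replacing withdrawn patients for want of study medication, while a Bonferroni split would need 22 or 23 included.

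The cost, apart from wording, is that blood pressure, GFR and FF lose stand-alone primary status, and an FF effect could not be claimed as confirmatory if ERPF is not significant.

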### **8.6 Univariate analysis**

In analyzing the outcome of the study, renal hemodynamics (GFR, ERPF, and FF) and volume status (ECV) are the primary endpoints. Effects of renal hemodynamics will be expressed as percent change from baseline. Effect of aliskiren and ramipril will be analyzed by paired-sample test and linear mixed effect model. Because of the cross-over design of this study, every patient will be their own control.

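### Section 8.6 names two analyses for the primary comparison without saying which decides, and uses a paired test and percent change from an undefined baseline where a period-adjusted model with baseline as covariate would be better

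*Protocol*

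**What the plan says.** Section 8.6 gives the analysis of the primary endpoints in two sentences. On scale: "Effects of renal hemodynamics will be expressed as percent change from baseline". On method: "Effect of aliskiren and ramipril will be analyzed by paired-sample test and linear mixed effect model". It does not rank the two methods, list model terms, or say whether baseline is the start of each period or the first visit. Section 8.7 adds a mixed model adjusted for other variables. Section 8.5 sets one two-sided threshold: P "less than 0.05 will be considered statistical significant".

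Renal hemodynamics are measured at the start and end of each period (Sections 3 and 7.3), so a baseline for each period is already collected. Sequence is randomised in blocks of 2 (Section 7.2).

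Section 4.4 works in absolute ml/min: "it was estimated that 14 patients had to complete the cross-over design sequence", in order "to give the study a 90% power to detect a statistically significant difference". It expects 10% dropout and enrols 16. Section 7.5 rules out replacement once treatment has started: "no new patients can be admitted to the study due to a limited availability of study medication".

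**The concern.** Four things follow from the wording of Section 8.6.

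- **No deciding analysis.** Two methods address one comparison at one threshold. They can differ when a patient has one period only, or when the model carries a period term or covariates.
- **Period.** A paired test has no place for a period term. A period effect on the analysed outcome goes into its error variance, and it biases the estimate if completers are unequal between sequences.
- **Incomplete patients.** The paired test discards a patient with one period, in a trial that expects dropouts and cannot replace them.
- **Percent change.** Subtracting each period's own baseline gives that second measurement a fixed weight of 1. Estimating the weight, with baseline as covariate, is at least as precise in large samples.

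With 14 planned completers, avoidable loss of precision matters most for GFR and FF, which have no sample size calculation.

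**Working it through.** **Inputs from the protocol.** Baseline ERPF SD 35; change 13 ± 11 ml/min on ACE inhibitor and 47 ± 17 on aliskiren; 14 completers; two-sided alpha 0.05; 90% power; blocks of 2. The protocol gives no correlations and no period effect, so those below are assumptions.

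**The plan's own figure.** The difference is 47 − 13 = 34 ml/min. A paired t-test (noncentral t) with an SD of 35 for the paired difference gives 89.5% power at n = 13 and 91.9% at n = 14, so 14 is reproduced. Using the quoted change SDs instead, with zero correlation, the SD of the difference is √(11² + 17²) = √410 = 20.25. Then 6 patients suffice, and power at 14 exceeds 99.9%.

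**Period effect.** Let π be the difference between periods in the analysed outcome. The aliskiren-minus-ramipril difference is then shifted by +π in one sequence and −π in the other. Simulation with SD 35, effect 34 and 14 completers (power for paired / period-adjusted; bias and type I error for the paired test only):

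| Completers | π (ml/min) | Power | Bias | Type I error |
|---|---|---|---|---|
| 7:7 | 0 | 91.8% / 91.5% | 0 | 4.9% |
| 7:7 | 17.5 | 86.9% / 91.6% | 0 | 3.0% |
| 7:7 | 35 | 69.3% / 91.6% | 0 | 0.6% |
| 8:6 | 17.5 | 91.5% / 91.0% | about 2.5 | 3.6% |
| 8:6 | 35 | 83.8% / 90.8% | about 5 | 1.4% |

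The bias is π × (8 − 6)/14 = π/7. At 8:6 it adds to the effect here, which partly offsets the lost power; with the opposite sign it would subtract.

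**Two P-values.** On complete pairs, a random-intercept model without a period term gives the same t statistic as the paired test. If the model has a period term and no period effect exists, taking whichever result is significant gives a type I error of about 5.5% instead of 5.0%.

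**Change against covariate.** Take baseline as the start of each period. Give the four visits a common variance s², correlation rw within a period and rb across periods.

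- Variance of the difference in change scores: 4s²(1 − rw).
- Variance of the difference in end values, after regression on the difference in baselines: 2s²[(1 − rb) − (rw − rb)²/(1 − rb)] = 2s²(1 − rw)(1 + rw − 2rb)/(1 − rb).
- Ratio: 2(1 − rb)/(1 + rw − 2rb), which is at least 1 whenever rw ≤ 1.

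Section 4.4 implies values of rw. A change SD of 11 gives 1 − 11²/(2 × 35²) = 1 − 121/2450 = 0.95. A change SD of 17 gives 1 − 289/2450 = 0.88.

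| rb (assumed) | Ratio, rw 0.951 | Ratio, rw 0.882 |
|---|---|---|
| 0.60 | 0.80/0.751 = 1.07 | 0.80/0.682 = 1.17 |
| 0.80 | 0.40/0.351 = 1.14 | 0.40/0.282 = 1.42 |

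The ratio reaches 2.0 only when rw = rb. The formula is for absolute change. With a baseline SD of 35 on a mean of 444 (35/444 = 8%), dividing by baseline should alter it little.

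**Why baseline must be defined.** If it means the start of each period, a shift in level that affects both ends of a period cancels from the change score, and only a period effect on the change itself matters. If it means the first visit, the common baseline cancels between treatments: the ratio above no longer applies, and a level shift does not cancel.

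**The case against.** The strongest reply is that much of this is normally settled in a statistical analysis plan, which may exist and is not shown. That stands for the mixed model. A reader might infer that it has no period term, but Section 8.6 lists no terms at all, so only the paired test certainly lacks one. The model can also keep patients with one period. The reply does not cover what the protocol itself fixes: a paired test, percent change, and two unranked methods.

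Three stronger readings are tempting and are not supported.

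- **That period effects make the result invalid.** Blocks of 2 balance the sequences, the paired test is unbiased at 7:7, and its type I error stayed below 5% at 8:6 in the cases with a period effect. The differing wash-outs in Section 3 (6 weeks, not mandatory for untreated patients, then 8 weeks) make different baselines plausible. A pure level difference cancels, however, if change is taken from each period's own start.
- **That percent change throws away a quarter to a half of the patients.** This needs variance ratios of 1.33 to 2.0, with similar correlations within and across periods. The SDs in Section 4.4 point to high within-period correlation and mostly smaller ratios.
- **That two P-values give wide scope for choice.** They coincide on complete pairs without a period term, and the inflation found is half a percentage point.

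It is also fair to read the percent-change sentence as describing presentation only. The text does not settle this.

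**Conclusion.** The point holds in a limited form. Section 8.6 leaves the deciding analysis open and the baseline undefined, and the paired test is a weaker choice than a period-adjusted model that uses baselines already collected.

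The period cost is mainly power, and only if a period effect on the analysed outcome exists: about 5 points at 17.5 ml/min and 22 points at 35 ml/min, for 7:7 completers with SD 35. Adjusting for period when there is no such effect costs about 0.3 points. Bias is small and needs uneven dropout.

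The loss from change scores is about 7% to 42% in variance. That rests on the SDs in Section 4.4, equal variances at all visits, an assumed rb of 0.60 to 0.80, and baseline meaning the start of each period.

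A reader might conclude that the ERPF comparison is underpowered, but the documents do not show this. If the change SDs of 11 and 17 hold, a period effect of 20 ml/min raises the SD to about √(410 + 400) = 28.5, and power for 34 ml/min with 14 patients is still about 98%. GFR and FF have no calculation, so no such reserve can be claimed for them.

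**What to change.** Name one deciding analysis in Section 8.6:

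- **Model.** A linear mixed model on the log end-of-period value, with fixed effects for treatment, period and sequence and a random patient effect.
- **Baseline.** Define it as the start-of-period measurement and enter its log as a period-specific covariate, together with the patient's mean baseline. For complete pairs the equivalent is to regress the between-period difference in end values on the between-period difference in baselines plus sequence. In the two-row mixed model, the baseline difference must not enter as a single patient-level covariate: it is constant across a patient's rows and cannot change the treatment contrast.
- **Patients.** All randomised patients with at least one treatment-period value.
- **Result.** The aliskiren/ramipril ratio with 95% confidence interval, which reads as a percent difference. On the log scale, mean effects on GFR, ERPF and FF also agree with FF = GFR/ERPF.
- **Supportive or descriptive only.** The paired test and percent change from baseline. Say also that the adjusted model of Section 8.7 is supportive.

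Add a line linking the log-scale analysis to the ml/min assumptions of Section 4.4.

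No new data are needed. The cost is a protocol text change and about two residual degrees of freedom: with 14 completers, 11 instead of 13, so the critical t rises from 2.16 to 2.20.
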